### Statistical analysis plan

The statistical analysis will be performed by an independent statistical expert blinded to the group allocation. SPSS V.26.0 (IBM) and R V.4.0.3 (R Foundation for Statistical Computing, Vienna, Austria) will be used for statistical analysis.

Each group will be summarised in terms of demographic characteristics and baseline variables. For comparisons of continuous variables, two-sample t-tests or Mann-Whitney U tests will be used, whereas for categorical variables, the χ^2^ test or Fisher’s exact test will be used.

As aforementioned, the primary outcome will be in SMM from the beginning to the end of the 12-week intervention. The independent two-sample t-test or Mann-Whitney U test will be used based on the distributional normality. We will make adjustments based on the covariates if there are significant demographic differences between the groups or if baseline variables differ significantly. In the primary analysis, the full analysis set (FAS) will be the main data set. Participants initially assigned to either group will be included in the FAS. However, our analysis will not use the data of ineligible participants (ie, those who are wrongly enrolled because of measurement or human error), subjects who received less than 75% of the planned intervention or subjects without the primary outcome measurement. For sensitivity analysis, we will use a protocol-specific set to compare with the results from the FAS. A per-protocol analysis will include participants who achieved the completion of the study without major deviations from protocol, who provided the primary outcome and who received at least 75% of the planned intervention. The rate of protocol compliance in each group will be calculated. A significance level of two-sided p<0.05 will be used. If needed, the multiple imputation method will be adopted for missing data.

We will use the same methods for analysing secondary outcomes as we did for analysing the primary outcome. A paired t-test or Wilcoxon signed-rank test will be used to assess the changes in outcome measures within groups before and after the intervention. To validate trend differences per visit, we will use repeated measures analysis of variance with post hoc tests.

Moreover, subgroup analysis will be done to identify whether gender or Asian Working Group on Sarcopenia-defined sarcopenia^30^ at baseline would affect the clinical response to HMB-enriched nutritional supplements.

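### The full analysis set drops low adherers and participants without the week-12 outcome, so the primary analysis is per-protocol in effect and the sensitivity analysis nearly repeats it

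*Protocol article*

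**What the plan says.** All of the following stands in the section Statistical analysis plan of the protocol article.

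- Primary data set: "In the primary analysis, the full analysis set (FAS) will be the main data set".
- Who is in it: "Participants initially assigned to either group will be included in the FAS".
- Who is then taken out: participants enrolled in error, and "subjects who received less than 75% of the planned intervention or subjects without the primary outcome measurement".
- Sensitivity analysis: "For sensitivity analysis, we will use a protocol-specific set to compare with the results from the FAS".
- The only other set defined: "A per-protocol analysis will include participants who achieved the completion of the study without major deviations from protocol". Two more conditions complete that definition, limiting it to those "who provided the primary outcome and who received at least 75% of the planned intervention".
- Missing data: "If needed, the multiple imputation method will be adopted for missing data".

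The section Primary outcome fixes the endpoint as the change in whole-body skeletal muscle mass (SMM) from baseline to week 12. Not having the primary outcome therefore means having no usable week-12 change.

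**The concern.** A full analysis set is meant to preserve the groups that randomisation created. Here the inclusion sentence does so and the next sentence undoes it. How much product a participant took, and whether they came back at week 12, are both settled after treatment starts.

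The two products differ in content: a blend of proteins, HMB, glutamine, konjac and fish oil against maltodextrin. Tolerance, and so adherence and attendance, could differ by arm. Progress on the diet could also influence who stays. Blinding does not close this route, because the product itself can affect adherence.

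At stake is whether the headline result is a randomised comparison at all. A sensitivity analysis would normally expose such a problem, but this one applies the same two exclusions. Close agreement between the two analyses would look reassuring without having tested anything.

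**Working it through.** **1. The two sets side by side**

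| Condition | FAS as written | Per-protocol set |
|---|---|---|
| Randomised | yes | yes |
| Not enrolled in error | required | not named (arguably covered by major deviations) |
| At least 75% of the intervention | required | required |
| Primary outcome present | required | required |
| Completed, no major deviation | not required | required |

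Both sets leave out anyone below 75% and anyone without a week-12 value. Apart from participants enrolled in error, they can differ only by people who took at least 75% and have a week-12 value, but who had another major deviation or did not count as completers. The term used for the sensitivity set is not formally equated with per-protocol, but no other set is defined.

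**2. Imputation**

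Everyone with a missing primary outcome is removed before analysis. For the primary endpoint, imputation can then act only on covariates.

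**3. How many could be excluded**

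The section Sample size estimation gives 25% attrition and 72 participants: 0.25 × 72 = 18, which leaves 54, or 27 per arm at 1:1. Participants who have an outcome but took less than 75% would be lost on top of that. The article gives no figure for them.

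**4. Possible bias (illustration)**

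Let p be the excluded fraction of the active arm and Δ the amount, in SD, by which the excluded do worse than the retained. Assume exclusion in the control arm is unrelated to outcome. If the whole active arm has mean 0 (no true effect) and the retained have mean m, then

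(1 − p)·m + p·(m − Δ) = 0, so m = p·Δ.

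The bias is p·Δ. The false-positive rate comes from the noncentral t distribution with 27 per arm, SD 1, two-sided 0.05, 52 degrees of freedom and noncentrality p·Δ·√(27/2).

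| p | Δ (SD) | Bias (SD) | False-positive rate |
|---|---|---|---|
| 0.25 | 0.5 | 0.125 | 7.4% |
| 0.25 | 1.0 | 0.25 | 14.7% |
| 0.25 | 1.5 | 0.375 | 27.2% |

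A simulation of 8,000 trials agrees: 7.7%, 14.2% and 27.6%.

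**5. The 75% rule on its own**

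Suppose only 5% or 10% of the active arm has a week-12 value but took less than 75% (an assumption), with the same range of Δ and 27 per arm. The bias is 0.025 to 0.075 SD or 0.05 to 0.15 SD. The false-positive rate is 5.1% to 5.8% or 5.4% to 8.4%.

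**The case against.** The contradiction in the text cannot be argued away, but several limits on its size and scope are fair.

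- **The figures cover all exclusions together.** The 25% is attrition, and most of those participants would probably have no week-12 value. Changing the definition does not recover their data, and imputation removes bias only as far as the variables used explain the dropout. The surely avoidable part is the smaller one in step 5. This stands.
- **The scenario is one-sided.** It makes exclusion informative in the active arm only, and always in that arm's favour. Nothing in the article supports that direction, and similar selection in both arms would largely cancel. This stands; the direction and size of the real bias are unknown.
- **Ineligibility is a different case.** Wrong enrolment is a fact that predates randomisation, even if it is found later. Excluding for it can be defended if the decision is blind. This stands, so the fault lies with the other two exclusions.
- **The sets are not identical, and imputation is not void.** The per-protocol set also requires completion and no major deviations, and imputation could still serve secondary outcomes and covariates. Both points are true, but neither gives an analysis that keeps non-adherers.
- **There are safeguards.** Assessors and the analyst are blinded, compliance is reported by group, and reasons for dropping out are recorded. Unequal exclusion would be visible, but nothing planned would correct for it.

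Nor is this a detail that an article may leave to a fuller document: the exclusions are stated outright.

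**Conclusion.** The plan is wrong as written and should be changed before analysis. A set that is called full and is said to contain assigned participants is restricted on adherence and on outcome availability. The per-protocol set repeats both restrictions, and the imputation provision has no missing primary outcome to work on. This follows from the definitions alone.

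The size is conditional. With 25% of each arm excluded and selection in the active arm only, bias runs from 0.125 to 0.375 SD and the false-positive rate from about 7% to 27% for Δ between 0.5 and 1.5 SD. The 75% rule alone would do less. Selection in the other direction would bias against the product.

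**What to change.** 1. Define the FAS as all randomised participants, analysed in the assigned arm whatever their adherence. Delete the 75% rule and the missing-outcome rule from it.
2. Allow exclusion for wrong enrolment only on information that predates randomisation, decided without knowledge of the arm.
3. For missing week-12 SMM, use multiple imputation within arm (baseline SMM, week-6 SMM, gender) or a mixed model for repeated measures. Table 1 already schedules bioimpedance at baseline, week 6 and week 12, so no new measurement is needed.
4. Keep the 75% criterion in the per-protocol set only, and name that set as the sensitivity analysis.

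The section Withdrawal criteria takes participants out of the trial, and the article does not say whether their week-12 measurement is still sought. Seeking it would reduce reliance on imputation, but the fix works without it.

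**Cost.** Revised wording and modest extra analysis. Keeping non-adherers may shrink the estimate. At the planned effect size of 0.93 (t-test, two-sided 0.05), power is 97.3% with 36 per arm and 91.8% with 27. If non-adherers dilute the effect by 25% (an assumption: 0.75 × 0.93 = 0.70), power is 83.1% with 36 per arm. If only 27 per arm also contribute data, it is 71.1%.

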#### Secondary outcomes

We will measure the following secondary outcomes:

The mean change in appendicular skeletal muscle mass, trunk skeletal muscle mass, total body fat mass (BFM), appendicular body fat mass, trunk body fat mass, basal metabolic rate, phase angle and BW from the beginning to weeks 6 and 12, as well as the mean change in whole-body SMM from the beginning to week 6, will be measured for all participants. These data will be measured using InBody 770 (Biospace).The mean change in HGS from the beginning to weeks 6 and 12 will be measured for all participants. A trained nurse will measure HGS using a digital handheld dynamometer (EH101; Xiangshan, Guangdong, China) to the nearest 0.1 kg according to the recommendation of the Chinese National Physical Fitness Evaluation Standard.^24^ The participants will be asked to perform three measurements for each hand, with rest periods of ≥30 s between each measurement. The HGS will be determined as the maximum value of the six records.The mean change in waist circumference and hip circumference from the beginning to weeks 6 and 12 will be measured for all participants. A trained nurse will measure the waist circumference using a tape at the level mid-way between the lower rib margin and the iliac crest with the participant breathing out gently. Hip circumference will be measured as the maximum circumference over the buttocks.^25^The mean change in physical activity from the beginning to weeks 3, 6, 9 and 12 will be measured for all participants using the self-reported International Physical Activity Questionnaire Short Form (IPAQ-SF).^26^The mean change in the score of the sit-to-stand test from the beginning to weeks 6 and 12 will be measured for all participants. A trained nurse will perform the 30 s sit-to-stand test,^27^ which is a classic test for measuring the performance of lower extremity muscles.The mean change in energy intake from the beginning to weeks 3, 6, 9 and 12 will be measured for all participants using the self-reported Food Frequency Questionnaire (FFQ).^28^The mean change of lipid profiles, fasting glucose, fasting insulin, HOMA-IR and albumin from the beginning to the end of the 12-week intervention will be measured for all participants.

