### Sample size estimation

To date, no studies have been done to determine whether HMB-enriched nutritional supplements are effective and safe for improving muscle mass and muscle function in obese adults during weight loss. To determine the sample size, we examined similar studies on HMB and referred to the study by Peng and Cheng that evaluated the effectiveness of HMB for improving SMM and quality in prefrail older adults.^12^ Using a 0.05 significance level, 80% statistical power and 25% attrition rate, a sample size of 70 has been assumed using an assumed effective size of 0.93. Moreover, to achieve a gender-balanced distribution within and between groups, a random stratification method including 36 samples per gender is proposed, adding up to 72 samples in total.

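### The supportive per-visit repeated-measures ANOVA drops, unless imputed, week-12 completers who missed an intermediate visit; a mixed model keeps them, but helps with dropout only if the analysis set is widened as well

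*Protocol article*

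**What the plan says.** Everything here is in the protocol article. Under Statistical analysis plan, the primary outcome, the change in SMM from baseline to week 12, is compared between groups once: "The independent two-sample t-test or Mann-Whitney U test will be used based on the distributional normality". Secondary outcomes are analysed in the same way. The course over visits then gets a further analysis: "To validate trend differences per visit, we will use repeated measures analysis of variance with post hoc tests".

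Two other sentences in that section decide who enters it. On missing data: "If needed, the multiple imputation method will be adopted for missing data". On the analysis set, data will not be used from ineligible participants, "subjects who received less than 75% of the planned intervention or subjects without the primary outcome measurement".

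Table 1 and Secondary outcomes give the visits. Body composition, grip strength and sit-to-stand are measured at weeks 0, 6 and 12; physical activity (IPAQ-SF) and energy intake (FFQ) at weeks 0, 3, 6, 9 and 12. Week-6 SMM is itself a secondary outcome: "as well as the mean change in whole-body SMM from the beginning to week 6, will be measured for all participants". Sample size estimation plans for "80% statistical power and 25% attrition rate".

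**The concern.** Classical repeated-measures ANOVA deletes a participant from the whole analysis if one visit is missing, whatever else was recorded. The more visits an outcome has, the more people are lost, so the five-visit questionnaires suffer most. The remaining complete cases represent the randomised groups only if visits are missing completely at random.

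The method is named in the plan, so this is not a detail left to a separate document. What is at stake is precision, and possibly selection, in the visit-by-visit description of a trial with about 54 expected completers. The data for a method that keeps incomplete cases will already have been collected.

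**Working it through.** **Inputs from the article.** 72 randomised 1:1; 25% attrition; one intermediate post-baseline visit for body composition (week 6) and three for IPAQ-SF and FFQ (weeks 3, 6, 9).

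**Assumed, not in the article.** Each intermediate visit is missed independently with probability p = 2%, 5% or 10%, and baseline is complete.

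**The plan's own figure.** The article gives no number for the visit analysis. Its sample size of 70 does not follow from its stated inputs: a two-sided t-test at effect size 0.93 with 80% power needs 20 per arm, and 40/0.75 = 53.3, so 54. That is a separate matter and in the safe direction. This check uses only 72 and 25%; that 54 also appears below is coincidence.

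**Step 1: expected week-12 completers.** 72 × 0.25 = 18 lost; 72 − 18 = 54. Completers who received less than 75% of the intervention would lower this further.

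**Step 2: completers lost to listwise deletion.** Loss = 54 × (1 − (1 − p)^k), where k is the number of intermediate visits.

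| p | Body composition, k = 1 | IPAQ-SF and FFQ, k = 3 |
|---|---|---|
| 2% | 54 × 0.020 = 1.1 | 54 × 0.059 = 3.2 |
| 5% | 54 × 0.050 = 2.7 | 54 × 0.143 = 7.7 |
| 10% | 54 × 0.100 = 5.4 | 54 × 0.271 = 14.6 |

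**Step 3: which rule removes whom.** At p = 5% the five-visit analysis keeps 54 × 0.857 = 46 of 72, so 26 are absent. Of these, 18 have no week-12 SMM and are removed by the analysis-set rule. Only about 8 are removed by the ANOVA.

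**Step 4: does a mixed model help, and on which set?** A simulation (1,500 runs per scenario, 36 per arm, weeks 0, 6 and 12) compared the week-12 contrast from complete cases with that from a likelihood-based model with unstructured covariance. Baseline was treated as a response. Assumed inputs: true difference 0.65 SD of change, correlation 0.7 between week-6 and week-12 change, 8% missed week-6 visits, and about 25% missing week 12. In the missing-at-random scenario, dropout depended on the week-6 change, in opposite directions in the two arms.

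| Set and missingness | Complete cases: estimate, power | Mixed model: estimate, power |
|---|---|---|
| All randomised, completely at random | 0.65, 0.61 | 0.65, 0.71 |
| All randomised, at random | 0.40, 0.29 | 0.65, 0.70 |
| Week-12 SMM required, completely at random | 0.65, 0.61 | 0.65, 0.66 |
| Week-12 SMM required, at random | 0.41, 0.29 | 0.41, 0.32 |

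On the plan's own set the mixed model gains a little power and leaves the bias where it was. The bias goes only when all randomised participants are kept. Its size depends on the chosen dropout pattern and is not a forecast for this trial.

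**The case against.** Several points against the concern are sound.

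- **Imputation may be used.** If multiple imputation is applied to this analysis, no completer need be dropped. That stands, but the sentence is conditional and does not say which analyses it covers. Imputation within the restricted set would fill only intermittent gaps.
- **The analysis is supportive.** The primary test and the between-group comparisons of secondary outcomes use t-tests or Mann-Whitney tests. This stands and limits the weight of the point.
- **Missed visits may be rare.** Data collection, management and monitoring provides for reminder calls, follow-up of missed sessions and weekly contact that includes both questionnaires. The low end of the range is therefore plausible.

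There are also stronger readings that a reader might infer and that the article does not support.

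- One might charge the ANOVA with discarding people who attend week 6 and leave before week 12, or with the whole fall from 72 to 46. The analysis-set rule removes those without week-12 SMM before any model is fitted.
- One might conclude that every longitudinal outcome is compromised. Changes to each visit are still compared by the two-sample tests.
- One might think that only a mixed model gives a treatment-by-visit contrast. Repeated-measures ANOVA with group as a between-subject factor gives one too.
- One might see a licence to pick the best visit in the post hoc tests. The primary time point is fixed at week 12 and the secondary time points are listed. Post hoc procedure and sphericity correction can properly be left to a fuller plan.

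**Conclusion.** The point holds in a limited form. The named method is a weak choice for these data: unless imputation is applied, it would remove about 8 of 54 expected week-12 completers from the IPAQ-SF and FFQ analyses (3 to 15) and about 3 from the body-composition analyses (1 to 5). These figures rest on the planned 25% attrition and on an assumed, independent 5% miss per intermediate visit (2% to 10% for the range).

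The larger loss, the 18 expected to lack week-12 data, comes from the analysis-set rule, so a change of model alone would not repair it. The primary result is unaffected. The change should be made because it costs little and gives a more defensible visit analysis.

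**What to change.** Replace the repeated-measures ANOVA sentence with:

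> Repeated outcomes will be analysed in all randomised participants with any post-baseline value by a linear mixed model with treatment, visit, treatment-by-visit, gender, baseline and baseline-by-visit, unstructured covariance and small-sample degrees of freedom. The week-12 treatment contrast is reported first, then earlier visits, with 95% CIs.

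Add that the exclusions for missing week-12 SMM and for less than 75% of the intervention do not apply to this analysis. Without that second statement, the change recovers only the intermittent misses.

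The cost is a change of wording and slightly more modelling work. No further data are needed, and both named packages (SPSS and R) fit the model. The remaining weakness is reliance on missing at random, which the data cannot confirm.

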## Ethics and dissemination

This trial has been registered on ClinicalTrials.gov (reference NCT04953936). This trial will be conducted following the Declaration of Helsinki.^31^ This study protocol was drafted according to Standard Protocol Items: Recommendations for Interventional Trials statement.^32^ It has been approved by the Biomedical Ethics Committee of West China Hospital (reference 2021-771). Any protocol amendments will be reapproved by the Biomedical Ethics Committee of West China Hospital and will be reflected in the participants’ informed consent form. We will obtain signed consent forms from all participants regarding the modification.

We intend to publish the results of this trial in appropriate academic peer-reviewed journals and conferences.

### Patient and public involvement

We did not involve patients or the public in the planning and design of this study.

## Discussion

This study will be a randomised, double-blind, parallel-group, placebo-controlled trial aiming to explore the effectiveness and safety of HMB-enriched nutritional supplements for improving muscle mass and muscle strength in obese adults during the weight loss process using calorie restriction. It will determine the feasibility of future large-scale clinical trials on HMB-based interventions for improving body composition (especially muscle health) in obese adults when performing weight loss plans.

The effectiveness of HMB for improving muscle mass and muscle strength has been well studied in athletes, healthy adults, older adults and patients with cancer.^33^ However, we found only two clinical trials addressing the effectiveness of HMB on muscle health in obese adults.^34 35^ In 2019, an RCT conducted in Iran demonstrated that supplementing with HMB for 6 weeks reduced weight, waist and abdominal circumference, and even increased strength without resistance training, and without affecting lean mass, in sedentary and overweight women.^34^ Most recently, Rondanelli *et al*^35^ conducted an RCT in obese or overweight Italian menopausal women. Using an oral nutrition supplement containing arginine, glutamine and HMB for 4 weeks, they observed that visceral adipose tissue and BFM were statistically significantly reduced, whereas fat-free mass (mainly muscle mass) remained the same.

Our trial has some strengths. First, it will be the first to evaluate the effectiveness of HMB-enriched nutritional supplements for improving muscle health in Chinese obese adults. Second, we will use a double-blinded design to minimise bias due to demand characteristics, the placebo effect and measurement bias. Last, we will focus on muscle mass and fat mass and muscle function (ie, HGS and physical performance).

This trial also has some limitations. First, this will be a single-centre trial and the sample size is relatively small. Therefore, the representativeness of our study sample may be limited. Second, participants in this study may be heterogeneous, given the wide age range. This heterogeneity should be considered when interpreting the results. Third, it might not be possible to completely control the dietary and physical activities of all participants. However, we will record the physical activity and energy intakes and will adjust for them as potential confounders. Fourth, the muscle mass and fat mass will be measured with a BIA device rather than a dual-energy X-ray absorptiometry (DXA) scanner. The hydration status of the participants may affect the results of the BIA. However, a recent study showed that DXA and segmental multifrequency BIA (InBody 770, which will be applied in this trial) were equally accurate for estimating muscle mass and fat mass.^36^

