#### Intervention group

The participants in the intervention group will receive oral HMB-enriched nutritional supplements (65 g, once daily) in powder form packaging in opaque plastic bottles, which include soybean isolate, protein, whey protein, casein, HMB, L-glutamine, wheat oligopeptide, medium-chain fatty acids, vitamin D, vitamin E, konjac powder and fish oil powder.

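### The Discussion commits to adjusting for physical activity and energy intake as confounders; if on-study values are meant, these are secondary outcomes, and the adjusted treatment effect can be biased in either direction

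*Protocol article*

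**What the plan says.** The commitment is in the limitations paragraph of the Discussion in the protocol article. It concedes that "it might not be possible to completely control the dietary and physical activities of all participants" and then says "we will record the physical activity and energy intakes and will adjust for them as potential confounders". It names no time point, outcome or model.

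The same two variables are listed under Secondary outcomes: "The mean change in physical activity from the beginning to weeks 3, 6, 9 and 12 will be measured for all participants", by the self-reported IPAQ-SF, and "The mean change in energy intake from the beginning to weeks 3, 6, 9 and 12 will be measured for all participants", by the self-reported FFQ. Table 1 schedules both questionnaires at baseline and at all four post-allocation visits. The section on data collection, management and monitoring also uses them in the weekly contacts to assess compliance.

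For the primary outcome, the Statistical analysis plan section says "The independent two-sample t-test or Mann-Whitney U test will be used based on the distributional normality". On covariates it says "We will make adjustments based on the covariates if there are significant demographic differences between the groups or if baseline variables differ significantly". It mentions neither activity nor intake.

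**The concern.** In a randomised trial, a confounder of the treatment comparison would have to be settled before allocation. Activity and intake at weeks 3 to 12 come after it. They may lie on the path from treatment to muscle mass, or share causes with it, such as motivation. An effect on intake is conceivable here: the active powder contains several proteins, medium-chain fatty acids and konjac, and the control is maltodextrin.

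Adjusting for such a variable changes the question. Any part of the effect that runs through it is taken out, and conditioning on it can create an association between arm and the unmeasured shared causes. The result no longer estimates the total effect of being assigned the supplement, yet the Discussion's wording would let it be presented as a comparison with confounding removed.

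**Working it through.** **Which values are meant.** The stated reason is incomplete control of diet and activity. Control can fail only once the 12-week intervention has begun, so baseline values would not address the limitation. The natural reading is on-study values, though this is inferred because no time point is given.

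**Inputs from the documents.** The plan states no figure for this adjustment, so there is none to reproduce. The check borrows the planning effect size of 0.93, the total of 72, 1:1 allocation, 25% attrition and the two-sided 0.05 level. This gives 72/2 = 36 per arm and 36 × 0.75 = 27 evaluable per arm. An exact t-test at 27 per arm and 0.93 SD has 91.8% power, the benchmark for the unadjusted rows below.

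**Assumed inputs.** The documents give none of these:
- *a*: shift in the on-study variable M caused by treatment, in SD (−0.5 to 0.5).
- *b*: direct slope of outcome on M (0 to 0.5).
- *u*: loading of M and of the outcome on a shared unmeasured cause (0, 0.4 or 0.5).

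**Formula.** With M at unit variance within arm, the within-arm slope of outcome on M is s = b + u². Adjusting for M then gives

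adjusted effect = total effect − a × s.

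**Results** (6,000 simulated trials per row, 27 per arm):

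| a | b | u | True total effect | a × s | Formula, adjusted | Simulated, adjusted | Rejection rate: unadjusted → adjusted |
|---|---|---|---|---|---|---|---|
| 0 | 0.3 | 0 | 0.93 | 0 | 0.93 | 0.93 | 92% → 94% |
| 0 | 0.3 | 0.4 | 0.93 | 0 | 0.93 | 0.93 | 92% → 96% |
| 0.3 | 0.3 | 0 | 0.93 | 0.09 | 0.84 | 0.84 | 92% → 87% |
| 0.5 | 0.3 | 0 | 0.93 | 0.15 | 0.78 | 0.78 | 92% → 80% |
| 0.5 | 0.5 | 0 | 0.93 | 0.25 | 0.68 | 0.68 | 92% → 77% |
| 0.5 | 0.3 | 0.4 | 0.93 | 0.23 | 0.70 | 0.70 | 91% → 76% |
| −0.5 | 0.3 | 0 | 0.93 | −0.15 | 1.08 | 1.08 | 92% → 97% |
| 0.5 | 0 | 0.5 | 0 | 0.125 | −0.125 | −0.13 | 5.1% → 7.7% |
| −0.5 | 0 | 0.5 | 0 | −0.125 | 0.125 | 0.12 | 4.9% → 7.0% |

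Formula and simulation agree. The unadjusted estimate and the estimate adjusted for the baseline value of M both stayed at the true effect in every row (0.93, or 0 in the last two). The simulation standard error of a 5% rejection rate is √(0.05 × 0.95/6000) = 0.28 percentage points, so 7.0% and 7.7% are not simulation noise.

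Three things follow. With a = 0 there is no bias, and adjustment even gains some precision. With a ≠ 0 the direction depends on the sign of a × s. With no true effect, a shared cause alone is enough to produce a spurious one.

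**The case against.** The strongest reply is that the harm is inferred. The sentence gives no time point, both questionnaires are also completed at baseline, and adjusting for baseline values would be sound. This stands as a limit on certainty. It does not remove the point, because the stated reason fits on-study values much better. On a baseline reading the two sections still differ: the Discussion adjusts unconditionally, the analysis section only after a significant imbalance.

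Second, a reader might infer that the trial's main result is biased, or that no randomised comparison is left. The documents do not support that: the primary test is an unadjusted t-test or Mann-Whitney U test. Only the adjusted analysis that the Discussion has in mind would be affected.

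Third, bias requires treatment to shift activity or intake, or how they are reported. No such shift is documented, both arms follow the same calorie-restriction rule, and participants are blinded. That makes a difference between arms less likely to arise from behaviour or expectation. It does not exclude an effect of the product itself on intake.

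Fourth, a reader might infer a one-sided loss of effect. The range includes zero, and a reversed shift inflates the estimate. Nor does self-report error by itself add bias: if it is the same in both arms it weakens the slope and shrinks the distortion.

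Finally, a reader might see a flat contradiction between the sections. The analysis section does not confine adjustment to baseline variables; it is silent on on-study ones. The sections are misaligned, not contradictory. Silence about detail would be no finding in a condensed article, but the Discussion states a method outright, and that method is the problem.

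**Conclusion.** The point holds in limited form. The Discussion commits to treating as confounders two variables that, on its most natural reading, are post-randomisation secondary outcomes. They cannot confound a randomised comparison, and adjusting for them can bias the estimated total effect if the supplement affects them.

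The size cannot be known from the documents. Over the assumed range, a true effect of 0.93 SD moved to anywhere from 0.68 (−0.25/0.93 = −27%) to 1.08 (+0.15/0.93 = +16%), with no movement when treatment leaves these variables unchanged. In the two scenarios with no true effect but a shared cause, the false-positive rate rose to 7.0% and 7.7%. These figures show what could happen; they are not predictions for this trial.

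The conclusion rests on the on-study reading, which is well supported but inferred. The unadjusted primary comparison is untouched. The correction is worth making because the sentence, as published, supports an adjusted analysis that could be mistaken for a cleaner estimate.

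**What to change.** Replace the sentence in the Discussion with:

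> Baseline physical activity and energy intake may be included as pre-specified covariates. On-study values will be summarised by arm as outcomes and will not be used as covariates in the primary or secondary efficacy comparisons. Any analysis adjusting for on-study values will be labelled exploratory (mediation).

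Bring the Statistical analysis plan section into line by saying there whether baseline activity and intake are pre-specified covariates and that on-study values are not used in the efficacy comparisons.

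The cost is a few sentences. Baseline IPAQ-SF and FFQ are already scheduled, so no new data are needed, and the sample size does not change. If the sponsor handles the change as a protocol amendment, the Ethics and dissemination section requires reapproval by the ethics committee.
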